
### Treatment arms

During the screening stage, patients with LAGC or GEJ adenocarcinoma will undergo baseline examinations, including enhanced CT scans of the stomach, pelvic cavity and chest (if necessary). After preliminary screening, patients who may meet the inclusion criteria will receive laparoscopic exploration or laparotomy, and all of them will receive abdominal exfoliative cytology concurrently. Patients without gross peritoneal seeding (P0) will be finally enrolled. Eligible patients were randomized to two arms: the arm of perioperative ChT and ICI with preoperative CRT (Arm A) and the arm of perioperative ChT and ICI (Arm B).

### Treatments

#### Chemotherapy

The SOX regimen consists of S-1 and oxaliplatin and is repeated every three weeks. Oxaliplatin will be administered intravenously at 130 mg/m^2^ on day 1. S-1 is administered orally at 40-60 mg twice a day for 14 consecutive days. Then, the patients will have a one-week rest period (Fig. 2). The dose of S-1 is according to the body surface area (BSA): patients with a BSA of less than 1.25 m^2^ receive 80 mg daily; those with a BSA of 1.25 m^2^ or more but less than 1.5 m^2^ receive 100 mg daily; and those with a BSA of 1.5 m^2^ or more receive 120 mg daily.

**Fig. 2 Fig2:**
[figure not shown]
The treatment schedule of Arm A and Arm B in the NeoRacing study

#### Chemoradiation

In Arm A, CRT will be given upfront. The radiotherapy (RT) consists of 45 Gy delivered in 25 fractions every five days per week for five weeks. The dose of concurrent ChT is 60 mg/m^2^ S-1 orally, oral tablets twice daily, on days 1-5 of each week (Fig. 2). RT planning is performed using computed tomography (CT) images with intensity-modulated radiotherapy (IMRT) or volumetric modulated arc therapy (VMAT). The RT field includes the primary lesion, involved regional lymph nodes, as well as the draining lymph nodes areas. Four-dimensional CT (4DCT) or passive breath gating (PBG) is adopted to eliminate the influence of the respiratory movement.

#### Surgery

Gastrectomy with standard D2 lymphadenectomy is recommended. The type of gastrectomy performed depends on the location and extent of the primary lesion. For GEJ or upper third tumors, a 3 cm esophageal margin is recommended, and a total gastrectomy or esophagogastrectomy is performed. For middle third tumors, the gastric margin is recommended to be more than 5 cm, and a total gastrectomy is performed. For lower third tumors, a 2 cm duodenal margin is recommended, and a subtotal or total gastrectomy is performed. Billroth I or Roux-en-Y gastrojejunostomy is performed for distal gastrectomy patients. Roux-en-Y esophagojejunostomy is performed for patients receiving total gastrectomy.

#### Immunotherapy

The immunotherapy includes perioperative treatment and postoperative maintenance treatment. The PD-1 mAb used in the study will be sintilimab, and the dose is 200 mg intravenously every three weeks. Regardless of which arm, the courses of immunotherapy that will be received by the enrolled patients are the same: 3 times preoperatively, 3 times postoperatively, and then maintained until one year after surgery.

### Efficacy, safety and toxicity evaluation

The efficacy evaluations include radiological and pathological evaluations. The radiological evaluation is based on an enhanced CT scan of the stomach. In Arm A, the tumor response evaluations are taken after CRT and when the preoperative treatment is completed. In Arm B, the tumor response evaluations are taken when the preoperative treatment is completed. All these evaluations are performed according to the Response Evaluation Criteria for Solid Tumors (RECIST) 1.1. The pathological evaluation is mainly used to evaluate the degree of tumor regression on the gross surgical specimens by judging the tumor regression grading (TRG) based on Ryan’s grading system [32].

Adverse events were assessed according to the Common Terminology Criteria for Adverse Event (CTCAE) v5.0. The evaluation of surgical complications is mainly based on the Clavien-Dindo classification.

### Follow-up

The follow-up of all patients will be carried out according to the protocol: every three months for at least two years, every six months for the third to the fifth year after surgery, and then every 12 months for life. The follow-up contents include the physical examination, tumor marker examination, and radiological examination. Ultrasounds and CT scans will be performed alternately every 6 months. Gastric endoscopy will be performed once a year.

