### Statistics

The EFS will be calculated from the date of randomization to the date of any event or censoring. The event is defined as below: (1) locoregional recurrence; (2) peritoneal seeding; (3) distant metastasis; (4) death of any reason; (5) tumor progression according to RESIST 1.1. The OS will be calculated from the date of randomization to the date of death or the date of the last follow-up. Survival will be estimated by using the Kaplan-Meier method, and differences between the survival curves will be examined with the log-rank test. Fisher’s exact test will be used to compare the patient characteristics between the two arms. Endpoints related to the rate, including the R0 resection rate, pathological response rate, toxicity occurrence, and surgical complications, will be compared between the two arms using the chi-square test. All statistical tests are two-sided. The level of significance is *P* < 0.05.

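### EFS runs from randomisation but follow-up scans are dated by surgery, so the arms share no assessment calendar and EFS is open to a probably small bias towards Arm A (minor)

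*Protocol article*

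**What the plan says.** - **Time origin (Statistics).** "The EFS will be calculated from the date of randomization to the date of any event or censoring". The events are locoregional recurrence, peritoneal seeding, distant metastasis, death from any cause and RECIST progression. The arms are compared by log-rank test.
- **Follow-up calendar (Follow-up).** Visits are "every three months for at least two years, every six months for the third to the fifth year after surgery", then yearly. On imaging: "Ultrasounds and CT scans will be performed alternately every 6 months".
- **Before surgery (Chemoradiation; Immunotherapy).** "In Arm A, CRT will be given upfront", with radiotherapy of "45 Gy delivered in 25 fractions every five days per week for five weeks". In both arms sintilimab is given every three weeks, "3 times preoperatively, 3 times postoperatively, and then maintained until one year after surgery".
- **Preoperative evaluations (Efficacy, safety and toxicity evaluation).** One arm has two evaluations: "In Arm A, the tumor response evaluations are taken after CRT and when the preoperative treatment is completed". The other arm has a single one: "In Arm B, the tumor response evaluations are taken when the preoperative treatment is completed". Radiological evaluation is by enhanced CT.

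The text gives neither the time from randomisation to surgery nor the number of preoperative SOX cycles per arm. The schedule is in Fig. 2, which was not available for this review.

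**The concern.** Four of the five EFS event types are usually dated by the assessment that reveals them. If the assessment dates differ systematically between arms on the EFS clock, the log-rank test compares calendars as well as treatments. Here the clock starts at randomisation and the scan calendar at surgery, and only one arm has a five-week course placed before the rest of its preoperative treatment.

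Two features add to this. The imaging sentence can mean CT every 6 months or, with the two methods alternating at 6-month steps, CT every 12 months. And a patient who never has surgery counts in EFS from randomisation but has no clearly stated scan clock.

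At stake is the reading of EFS, which bears on whether a gain in pCR carries over into longer-term benefit. The Discussion names that as the open question.

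**Working it through.** **1. The plan's own figure.** The only computed design figure is the pCR sample size. With unpooled variance, n per arm = (1.645 + 0.842)² × (0.26×0.74 + 0.10×0.90) / 0.16² = 68.2, so 69 per arm. Then 138 × 1.1 = 151.8, so 152, or 76 per arm. This reproduces the plan. The EFS point uses only the 76 per arm.

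**2. The surgery lag (assumption).** Suppose the preoperative period is set by three three-weekly sintilimab doses and the gap to surgery is the same in both arms.
- Arm B: 3 × 3 = 9 weeks.
- Arm A, one dose within chemoradiation: 5 + 2×3 = 11 weeks.
- Arm A, all three doses after chemoradiation: 5 + 3×3 = 14 weeks.

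The lag is then 2 to 5 weeks.

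**3. Average detection delay.** Take surgery at week 13 in Arm B and week 18 in Arm A, with CT every 26 weeks after surgery. Arm B is scanned at weeks 39, 65 and so on; Arm A at weeks 44, 70 and so on. In each 26-week cycle:
- disease arising in the 5 weeks between an Arm B scan and the next Arm A scan is found 65 − 44 = 21 weeks earlier in Arm A;
- disease arising in the other 21 weeks is found 44 − 39 = 5 weeks later in Arm A.

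With even onset these cancel: 5 × 21 = 21 × 5. A simulation agrees. Mean delay in Arm A minus Arm B was −0.03 to +0.05 months without the post-chemoradiation scan, and −0.08 to −0.21 months with it (lags of 2 to 8 weeks).

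**4. Why the log-rank test still moves.** At each Arm B scan both arms have been through the same number of earlier follow-up scans. At each Arm A scan, Arm B has been through one more, so its risk set is already depleted and the expected count for Arm A is too high. Illustration with rigid dates, median EFS 30 months (assumed), 6-monthly CT and no deaths dated exactly:
- events per arm at the first scan: 76 × (1 − 2^(−6/30)) = 9.84;
- expected in A: 9.84 × 76/152 + 9.84 × 76/(76 + 66.16) = 4.92 + 5.26 = 10.18;
- observed minus expected: 9.84 − 10.18 = −0.34; variance 2.32 + 2.29 = 4.61;
- HR ≈ exp(−0.34/4.61) = 0.93.

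Scatter in surgery and visit dates blurs this ordering, and exactly dated deaths dilute it, so a realistic figure lies nearer 1.

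**5. Simulation under no true difference.** 76 per arm, median 30 months, censoring uniform over 24-48 months, lag 2-5 weeks, dates scattered by one to two weeks or so:

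| Detection interval | Apparent HR, A vs B | Significant in favour of A (nominal 2.5%) |
|---|---|---|
| 3 months | 0.99-1.00 | 2.2-3.0% |
| CT every 6 months | about 0.96-1.00 | about 3-4% |
| CT every 12 months | about 0.90-0.98 | about 3-7% |

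With no lag the HR is 1.00.

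**6. Sensitivity.**
- *Exact dates.* With 20% of events dated exactly, the HR is about 0.97-0.98 (6-monthly) and 0.94-0.96 (12-monthly).
- *Extra Arm A scan.* Adding a week-6 scan at a 5-week lag changes the HR from 0.963 to 0.965 (6-monthly) and from 0.909 to 0.911 (12-monthly).
- *Censoring rule.* The table censors at the end of observation. A separate run with median 24 months, 20% of events dated exactly and event-free patients censored at their last scan gave 0.90-0.98 (6-monthly) and 0.94-1.00 (3-monthly), the lowest values with rigid dates. Changing only the censoring rule in the model of step 5 also moves the HR further from 1, most of all with 12-monthly CT.

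**The case against.** The strongest case on the other side has five parts.

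- **The lag is not in the text.** This stands. Later surgery in Arm A is an inference from upfront chemoradiation with treatment still to follow, and its length is unknown. The direction is likely because equal timing would need compensating scheduling that the article does not describe.
- **Arm A is scanned once more before surgery.** This works the other way, because early progression can be recorded sooner in Arm A. It stands as a fact, but the scan catches few events and barely changes the HR. It is also a second inequality between the calendars.
- **Events can surface outside the CT grid.** This stands in part. Deaths are dated exactly, visits are three-monthly with examination and tumour markers, and endoscopy is yearly. If events are in effect detected every 3 months, the bias all but disappears.
- **The surgery anchor may be over-read.** In the Follow-up sentence the words on surgery sit with years three to five, and the schedule is said to cover all patients. The natural reading still counts the whole sequence from surgery. How unresected patients are followed may be in the full protocol, which is not shown, so I treat that as something to settle in the same edit and not as a separate fault.
- **EFS is secondary in a trial sized for pCR.** This stands and sets the severity.

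A reader might go further and infer that the same disease is systematically recorded later in Arm A. The documents do not support that. A shifted grid finds some disease later and some earlier, and on average the delay is about equal, or slightly shorter in Arm A once its extra scan is counted.

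**Conclusion.** The point holds as a minor one. EFS is timed from randomisation, follow-up assessments are dated by surgery, and the preoperative courses and evaluations differ by arm. The arms therefore lack a common assessment calendar, and EFS is open to assessment-time bias, probably small and towards Arm A.

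The size rests on assumptions the article cannot confirm: the 2-5 week lag, exponential EFS, the scatter in dates, the share of events dated exactly, and censoring at the end of observation. Under these the apparent HR with equal treatments is about 0.96-1.00 for 6-monthly CT and about 0.90-0.98 for 12-monthly CT. It would be further from 1 if event-free patients were censored at their last scan. The pCR comparison and the sample size are not touched.

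**What to change.** In the Follow-up section:

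1. Schedule the CTs used for EFS at the same weeks from randomisation in both arms, and for all randomised patients, including those not resected.
2. State that CT at one fixed interval is the EFS assessment and that ultrasound is additional. This also resolves the ambiguous imaging sentence.
3. Leave postoperative clinic visits tied to surgery.

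With equal assessment times the simulated HR returns to 1.00.

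The cost is an amendment to the assessment calendar, with some scans moving by a few weeks relative to clinic visits. The number of CTs rises only if the present intent is CT every 12 months and the sponsor chooses every 6 months. No treatment changes.

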### Sample size calculation

The preliminary analysis of the PREACT study (NCT03013010) showed that preoperative chemotherapy with three cycles of the SOX regimen can yield a pCR rate of 2%, and two cycles of the SOX regimen plus chemoradiation of 45 Gy/S-1 yielded a pCR rate of 17%. The preliminary analysis of a study called NeoPLANET (NCT03631615) showed that the pCR rate of CapeOX plus camrelizumab combined with chemoradiation was 26.7% (4/15). According to poster 4036 of 2021 ASCO, four cycles of mFOLFOX6 plus camrelizumab yielded a pCR rate of 10% (5/52). Thus, with the addition of PD-1 mAb, the increased range of the pCR in both the preoperative ChT group and CRT group was approximately 8 to 10%, which is a reasonable range. Based on these research data, in this study, the pCR rate of Arm A is set as P1 = 26%, and the pCR rate of Arm B is set as P2 = 10%. The null hypothesis (H0): the pCR rate of Arm A is not better than that of Arm B, that is, P1-P2 ≤ 0. The alternative hypothesis (H1): the pCR rate of Arm A can be increased by 16% compared with Arm B, that is, P1-P2 = 16%.

The patients were randomly assigned to two arms at a ratio of 1:1. One side test is adopted, and if the error rate of type I (α) is set to 0.05, then 138 patients need to be enrolled, i.e., 69 in each arm, which can ensure that the test efficiency (1-β) reaches 80%. When the dropout rate is set to 10%, 152 patients are needed, with 76 in each group.

### Statistics

The EFS will be calculated from the date of randomization to the date of any event or censoring. The event is defined as below: (1) locoregional recurrence; (2) peritoneal seeding; (3) distant metastasis; (4) death of any reason; (5) tumor progression according to RESIST 1.1. The OS will be calculated from the date of randomization to the date of death or the date of the last follow-up. Survival will be estimated by using the Kaplan-Meier method, and differences between the survival curves will be examined with the log-rank test. Fisher’s exact test will be used to compare the patient characteristics between the two arms. Endpoints related to the rate, including the R0 resection rate, pathological response rate, toxicity occurrence, and surgical complications, will be compared between the two arms using the chi-square test. All statistical tests are two-sided. The level of significance is *P* < 0.05.

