Positive peritoneal lavage cytology without visible gross peritoneal metastasis (CY1P0) is a special type of distant metastasis of GC, which is defined as stage IV disease in the American Joint Committee on Cancer (AJCC) guidelines for GC (8th edition) [17] and in the Japanese Classifications of Gastric Carcinoma [18]. It has been reported to be a key predictor of peritoneal dissemination [19] and poor prognosis [20–23]. Currently, the therapeutic strategies for GC with CY1P0 have not been fully defined [24]. Typically, palliative chemotherapy has been widely accepted as the standard therapy for stage IV GC patients globally [25, 26]. Moreover, curative-intent surgery was not indicated in GC patients with CY1 according to the treatment algorithm in the Japanese gastric cancer treatment guidelines [25]. However, radical surgery followed by postoperative chemotherapy is one of the most widely accepted therapeutic strategies for GC patients with CY1 in clinical practice and was established by a phase II trial called the CCOG0301 study [27, 28]. In addition, preoperative chemotherapy as an initial treatment for GC patients with CY1 is considered a promising treatment strategy, as systemic chemotherapy could eliminate the limited metastatic disease in some patients, could convert the metastatic disease to resectable disease and could achieve long-term survival after curative surgery [20, 29–31]. Therefore, there are currently no widely accepted treatment guidelines for CY1P0 GC patients.

Based on the above background, we designed this study, aiming to evaluate the safety and efficacy of perioperative SOX plus sintilimab with/without preoperative CRT. The study protocol of this trial, which has the acronym NeoRacing, is described in this article.

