## Methods

### Study design

NeoRacing is a randomized phase II trial carried out at Fudan University Shanghai Cancer Center (FUSCC) in China. The study can be divided into the screening stage, treatment stage and follow-up stage. The enrolled patients will receive perioperative SOX chemotherapy, PD-1 antibody (sintilimab) and radical surgery, with or without preoperative CRT (Fig. 1). The patients were randomized by stratified permutated block randomization on a web-based system. The status of peritoneal cytological examination (CY0 vs. CY1) was the stratification factor. The study protocol was approved by the Ethics Committee of FUSCC. All patients provided written informed consent before recruitment. Monitoring will be carried out in this trial.

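### The log-rank test for EFS and OS does not mention cytology, the only randomisation stratum; stratifying by it would recover a modest amount of power at no cost

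*Protocol article*

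**What the plan says.** - **Randomisation** (Protocol article, Study design): stratified permuted blocks. "The status of peritoneal cytological examination (CY0 vs. CY1) was the stratification factor". No other factor is named.
- **Prognosis** (Background): positive cytology without visible peritoneal disease is classed as stage IV. "It has been reported to be a key predictor of peritoneal dissemination [19] and poor prognosis". No hazard ratio is given.
- **EFS and OS** (Statistics): Kaplan-Meier estimation, and "differences between the survival curves will be examined with the log-rank test". Peritoneal seeding is one of the listed EFS events. Neither strata nor covariates are mentioned, and no hazard ratio or regression model is planned.
- **Rate endpoints** (Statistics): these "will be compared between the two arms using the chi-square test", again with no mention of strata.
- **Status of the endpoints** (Secondary endpoints; Sample size calculation): EFS and OS are secondary, and the sample size rests on pCR alone.

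**The concern.** A factor is usually chosen for stratified randomisation because it is expected to drive outcome, and the protocol says so for cytology. By its own account the factor even predicts one component of EFS, peritoneal seeding.

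Once the arms are balanced within CY0 and within CY1, the difference in prognosis between the strata no longer contributes to chance differences between the arms. An unstratified log-rank test still computes its variance as if it did. It therefore rejects less often than its nominal level under the null hypothesis and has less power under the alternative.

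At stake is some sensitivity on EFS and OS. The Discussion names survival benefit as the question still to be answered, and the article states no power for either endpoint.

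**Working it through.** **1. The plan's own figure.** Inputs from Sample size calculation: pCR 26% against 10%, one-sided α 0.05, power 80%. With unpooled variance:

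n per arm = (1.645 + 0.842)² × (0.26 × 0.74 + 0.10 × 0.90) / 0.16² = 6.18 × 0.2824 / 0.0256 ≈ 68.2, rounded up to 69.

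This gives 138 in total, and 138 × 1.1 = 151.8, so 152. The stated figures reproduce. They concern pCR only; there is no EFS or OS figure to reproduce.

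**2. Inputs for EFS/OS.** From the document: N = 152, 1:1 allocation, balance within CY strata, two-sided 0.05 ("All statistical tests are two-sided"). Assumed, because the document does not give them:

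- control median of 36 months in CY0, exponential survival;
- 24 months of accrual and at least 36 months of follow-up;
- true within-stratum treatment hazard ratio (HR) of 0.60;
- CY1 share of 5–33%;
- CY1-to-CY0 HR of 2 to 5.

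The Discussion gives one guide to the CY1 share: about one-third of potentially eligible patients in the centre's earlier randomised trial were P1 or CY1 combined. P1 patients are excluded here. If that third split evenly, CY1 would be (1/6)/(5/6) = 20% of the remainder. If it were all CY1, the share would be 33%, which is the ceiling.

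**3. Test statistics.** With dᵢ the event indicator, gᵢ the arm and pᵢ the proportion of those at risk in that arm:

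- U = Σ dᵢ(gᵢ − pᵢ), V = Σ dᵢ pᵢ(1 − pᵢ), Z = U/√V
- stratified: Z = (U₀ + U₁)/√(V₀ + V₁), with U and V computed within CY0 and within CY1
- approximate log HR = U/V, using the stratum sums for the stratified version

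**4. Results** (4,000 simulated trials per setting, both tests applied to the same data, about 80–100 events):

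| CY1 share | CY1 HR | Power, unstratified | Power, stratified | Loss (points) | HR, unstratified / stratified |
|---|---|---|---|---|---|
| 5% | 2 | 61.9% | 62.3% | 0.4 | 0.60 / 0.60 |
| 10% | 2 | 61.1% | 62.5% | 1.4 | 0.60 / 0.60 |
| 10% | 3 | 59.5% | 62.9% | 3.4 | 0.62 / 0.60 |
| 20% | 2 | 61.9% | 63.7% | 1.8 | 0.61 / 0.60 |
| 20% | 3 | 59.1% | 65.9% | 6.8 | 0.63 / 0.60 |
| 33% | 2 | 64.0% | 67.0% | 3.0 | 0.61 / 0.60 |
| 33% | 3 | 61.8% | 70.9% | 9.1 | 0.63 / 0.59 |
| 33% | 5 | 49.8% | 71.1% | 21.3 | 0.68 / 0.59 |

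Under the null, with a CY1 HR of 2 to 5, the unstratified test rejects in 2.8–4.9% of trials and the stratified test in 4.7–5.5%. If cytology is not prognostic at all, the two powers differ by at most 0.4 points, so stratifying costs nothing visible.

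A second simulation (3,000 trials per setting, uniform censoring at 22–50 months, CY1 HR 3) shows the same pattern: 54% against 60% at a 20% CY1 share, and 55% against 63% at 30%. With a 10% share, or a CY1 HR of 2, the gain is 0–3 points.

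**5. Rate endpoints.** For pCR at 69 per arm, chi-square and a CY-stratified Cochran-Mantel-Haenszel (CMH) test differ by at most 1.5 points of power over CY1 shares of 10–33%. The largest gap is 70.5% against 72.0%, two-sided, with a 33% share and a CY1 odds ratio of 0.2. One-sided, both tests have about 81–82%.

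**The case against.** The strongest reply is that the article never says unstratified. It is a condensed account, and whether a named test is stratified is often settled in an analysis plan, which is not shown. That stands as a caution: a reader might infer that the trial will certainly ignore the stratum, and the text does not prove it. But the Statistics section does name the tests, their sidedness and the significance level, and a log-rank test named without qualification is ordinarily read as unstratified. If the full plan already stratifies, one phrase closes the point.

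Three stronger readings are tempting and are not supported:

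- **That the primary analysis suffers.** The chi-square test is not used for EFS or OS, and for pCR it loses almost nothing. The extra condition for CY1 patients (conversion to CY0) still leaves one yes/no outcome per patient, and with allocation balanced on cytology the simple difference in rates is unbiased. The chi-square test is not an error.
- **That the planned effect estimate is shrunk.** No hazard ratio is planned. If an unadjusted one were reported, it would sit slightly nearer 1, because a marginal and a within-stratum hazard ratio are different quantities. The Kaplan-Meier curves remain valid marginal estimates.
- **That the test is invalid.** The error is on the conservative side; false positives are not inflated.

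It is also fair that EFS and OS carry no power claim, and that under these assumptions power is well below 80% with either test.

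**Conclusion.** The point holds in a limited form. Read as written, the log-rank comparison of EFS and OS leaves out a stratum that was balanced by design and that the protocol calls prognostic. The result is a valid but conservative test with somewhat less power than the same data could give.

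For a true HR of 0.60, the loss is about 1–7 points when CY1 is 10–20% of patients with a prognostic HR of 2–3. It is close to nil if CY1 is rare or weakly prognostic. It reaches 9 points at a one-third share with HR 3, and about 21 points in the extreme case of HR 5. The direction is firm. The size rests on the assumed CY1 share, CY1 hazard, treatment effect and follow-up.

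An unadjusted HR, if one were reported, would be about 0.62–0.63 instead of 0.60 at a prognostic HR of 3. The pCR sample size and the primary conclusion do not change. This is a free improvement to secondary analyses, not a flaw in the trial's main inference.

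**What to change.** - State in the analysis plan, before outcome data are compared by arm, that EFS and OS will be tested with a log-rank test stratified by CY status at randomisation (CY0, CY1).
- If a hazard ratio is reported, take it from a Cox model stratified in the same way.
- Show the unstratified log-rank result as a sensitivity analysis.
- Optionally, for consistency with the design, use a CY-stratified CMH test with a stratified risk difference for pCR and the other efficacy rates. No material gain in power should be claimed for it.

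The cost is wording only. CY status is already recorded for every randomised patient, and neither new data nor more patients are needed.

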### Explorative endpoints

The association of the baseline PD-L1 comprehensive positive score (CPS), tumor mutation burden (TMB), mismatch repair (MMR) status, and EBER with the efficacy of immunotherapy will be assessed.The association between the gut microbiota and the efficacy of immunotherapy will be assessed.The association between the *Helicobacter pylori* (HP) infection status and the efficacy of immunotherapy will be assessed.The influence of the preoperative therapy on the tumor immune microenvironment (TIME) and the systemic immune status will be assessed.

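### Baseline characteristics are significance-tested and the named outcome tests are unadjusted, although CY status and baseline markers are available: a small loss of precision, not a bias

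*Protocol article*

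**What the plan says.** Under Statistics, the protocol article says that Fisher's "exact test will be used to compare the patient characteristics between the two arms". The next sentence says that rate endpoints "will be compared between the two arms using the chi-square test". It lists R0 resection, pathological response, toxicity and surgical complications. pCR is not named there but belongs to the same class. Survival curves are compared with a log-rank test. No covariate or stratum is attached to any of these tests.

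Study design describes stratified permuted-block randomisation on a web-based system, with cytology status (CY0 or CY1) as the stratification factor. The primary endpoint is defined differently for CY0 and CY1 patients. Explorative endpoints lists the "baseline PD-L1 comprehensive positive score (CPS), tumor mutation burden (TMB), mismatch repair (MMR) status, and EBER" for association with the efficacy of immunotherapy. The Discussion says that the value of these markers is still disputed and that the trial will validate them further.

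**The concern.** Two choices are stated in the text.

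- **Testing baseline balance.** The arms are formed by randomisation, so the null hypothesis of the Fisher test is true by design. Its P value cannot show whether an imbalance matters, because that depends on how strongly the characteristic predicts outcome. An imbalance in a strong predictor can be non-significant, and one in an irrelevant characteristic can be significant.
- **Unadjusted outcome tests.** The trial has a stratification factor that also enters the pCR definition, and it lists baseline markers that may predict response. Where such covariates do predict pCR, a prespecified adjusted estimate is more precise than the raw difference. With only about 25 pCRs expected, some precision may be worth having.

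**Working it through.** **Inputs from Sample size calculation.** "the pCR rate of Arm A is set as P1 = 26"%; "the pCR rate of Arm B is set as P2 = 10"%; 1:1 allocation; one-sided α = 0.05; power 80%; 69 per arm, raised to 76 for dropout.

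**The plan's own figure.** With the unpooled normal approximation,

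n = (1.645 + 0.842)² × (0.26×0.74 + 0.10×0.90) / 0.16² = 68.2, so 69 per arm. This reproduces the plan.

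**Events and standard error at 69 per arm.** Expected pCRs are 69×0.26 + 69×0.10 = 17.9 + 6.9 = 24.8. The standard error of the difference is √[(0.1924 + 0.09)/69] = 0.064, or 6.4 points.

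**How often the baseline test would be significant.** Fisher's test is conservative. Exact enumeration at 76 per arm, summing binomial probabilities over all tables with P < 0.05, gives a false-positive rate of about 1.5% at a prevalence of 5% and about 3.3% at 30%.

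**Effect of chance imbalance.** For an assumed marker prevalence of 10%, one SD of the difference in prevalence between arms is √(2×0.10×0.90/69) = 5.1 points. If marker-positive patients have a pCR rate 30 to 40 points higher (assumed), the observed pCR difference moves by 0.051×30 to 0.051×40, about 1.5 to 2 points. The standard error of 6.4 points already includes this variation. Over simulated trials the unadjusted difference averages 0.160 in every setting, so it is unbiased.

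**Adjusting for one binary marker.** Simulation of 100,000 trials per setting, 69 per arm, with marginal pCR held at 26% and 10%. The unadjusted chi-square test is compared with a Cochran-Mantel-Haenszel test. Assumed prevalence is 5% to 50%; each range runs over prevalence.

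| Assumed odds ratio for pCR | Stratified power, one-sided 5% | Stratified power, two-sided 5% |
|---|---|---|
| 1 | 80% | 70% |
| 2 | 80–81% | 70–71% |
| 3 | 81–82% | 70–72% |
| 5 | 81–83% | 71–74% |
| 10 | 83–86% | 73–78% |

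Unadjusted power is about 81% one-sided and 70% two-sided. Both are shown because Sample size calculation says "One side test is adopted, and if the error rate of type I (α) is set to 0.05" while Statistics says "All statistical tests are two-sided"; that conflict is a separate matter. Under the null, one-sided type I error is 5.1–5.3% unadjusted and 4.8–5.1% stratified.

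**Adjusting for two markers.** Simulation of 8,000 trials per setting, linear model with robust standard error, one-sided 5%. Assumed: 12% MMR-deficient or EBER-positive, 50% CPS-high.

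| Assumed odds ratios | Power unadjusted → adjusted | Variance ratio |
|---|---|---|
| 1 and 1 | 81.5% → 80.7% | not given |
| 4 and 1.5 | 81.2% → 82.0% | 0.952 |
| 6 and 2.5 | 80.9% → 83.6% | 0.909 |
| 10 and 3 | 81.2% → 85.8% | 0.882 |

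Adjusted type I error is 4.7–5.5%. A further check with 15% of marker values missing also showed a loss of about 1 point when the markers are uninformative.

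**Not computed.** The documents give neither the CY1 proportion expected among enrolled patients nor its effect on pCR, and no event numbers for EFS or OS. No figure is offered for these.

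**The case against.** The strongest reply is that nothing in the primary inference is wrong. A reader might infer that a chance imbalance in MMR or EBER biases the pCR comparison, or that the plan gives up free power. The documents support neither reading. Randomisation makes the unadjusted difference unbiased, and its standard error already allows for imbalance. The gain in power depends on marker prevalence and strength that the article does not give. At odds ratios of 3 or below it is negligible, and for uninformative markers it is slightly negative. The Discussion calls these markers disputed, so studying them as exploratory is coherent.

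It can also be said that covariate lists and supportive models usually sit in the full protocol or analysis plan, which is not shown. That is fair: the article does not exclude adjusted analyses, and their absence alone would be no finding. Nor does it attach any decision to the Fisher results, so a reader who infers that they will drive a later choice of covariates goes beyond the text. Deleting those tests would change no estimate.

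With about 25 pCRs, about 7 of them in Arm B, a logistic model with several markers and missing categories would be sparse. This also stands, and it limits both the list and the method.

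What survives is narrower. The Fisher tests and the unadjusted outcome tests are stated, not merely unmentioned. The stated tests also ignore the trial's own stratification factor, the covariate that the design supports best.

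**Conclusion.** The point holds as a minor one. Significance tests of baseline characteristics between randomised arms are uninformative, and the named outcome tests use neither CY status nor the listed markers. The consequence is a possible loss of precision, with no bias and no inflation of type I error. Under assumed prevalences of 5% to 50% and odds ratios of 1 to 10, adjustment changes one-sided power by about -1 to +5 points (about 0 to +7 two-sided). The gain becomes noticeable only from an odds ratio of about 3 to 5 upwards. All marker prevalences and odds ratios are assumptions; only the pCR rates, α and sample size come from the protocol article.

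**What to change.** 1. Replace the Fisher tests with a descriptive baseline table by arm, without P values.
2. Before outcome data are reviewed, prespecify a pCR risk difference adjusted for or stratified by CY status, plus a short marker list: MMR/EBER status and CPS group, with a category for missing values. Use a linear model with robust standard error, or a similar method that copes with about 25 events. Apply it whatever the observed balance.
3. Keep the unadjusted chi-square test as a sensitivity analysis.
4. For EFS and OS, use a CY-stratified log-rank test or a Cox model with the same covariates.

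The cost is analysis wording, since the covariates are already listed for baseline assessment; the article does not say how complete the marker data will be. The statistical downside is about 1 point of power if none of the covariates predicts pCR, and the list must stay short.
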